### Blinding

2.11

Trial interventions will not be blinded for investigators, clinicians and patients, as this is not considered feasible. Mortality assessments will be registry‐based where possible. The statistical analyses of all secondary outcomes will be done first, with the intervention groups masked, i.e., randomly coded as 0 and 1, and without data extraction on the primary outcome, as this would likely reveal trial allocation for most patients. Afterwards, data on the primary outcome will be extracted, and the primary statistical analysis of this will be conducted, also with allocations masked. All supplemental analyses will be conducted without blinding of statisticians.

### Data Registration and Monitoring

2.12

All data will be entered into a central web‐based, password protected, encrypted eCRF constructed in Research Electronic Data Capture (REDCap) hosted in the North Denmark Region [38, 39]. All patients will undergo centralised day‐to‐day monitoring by the sponsor or delegate following a defined monitoring plan, according to the International Conference on Harmonisation of technical requirements for registration of pharmaceuticals for human use GCP (ICH‐GCP) standards [40].

### Safety and Adverse Events

2.13

Selected serious adverse events possibly related to the intervention, as defined under secondary clinical outcome (e), will be registered daily during ICU admission in the eCRF. Similar events occurring after discharge from the ICU will be captured in the eCRF in the 90‐day follow‐up form. When a pneumothorax or haemothorax is registered in the eCRF, an automatic e‐mail notification is sent to the sponsor and delegate, who, together with local investigators, will review each event to assess potential causality between the event and the intervention. Other serious adverse events according to ICH‐GCP definition [40], not defined under secondary clinical outcome (e), as well as non‐serious adverse events, will not be systematically recorded, but will be evaluated continuously by primary site investigators and co‐investigators in their daily clinical practise. If an unexpected serious adverse event occurs, i.e., not defined under secondary clinical outcomes (e), which local investigators consider potentially related to the intervention, sponsor or delegate will be contacted as soon as possible, and potential causality will be assessed. As this is a small, low‐risk feasibility trial, with no pre‐planned interim analyses, no formal data monitoring and safety committee will be established, ongoing safety oversight will be conducted by the investigators and sponsor as described.

### Statistics

2.14

#### Sample Size Calculation

2.14.1

To detect or reject an expected minimum of 75% relative increase (an absolute increase of 30% points) in patients receiving pleural drainage in the intervention group, and assuming a maximal incidence of pleural drainage in the ICU within 90 days of 40% in the control group, with a type 1 error risk (two‐sided α) of 0.05 and a type 2 error risk (*β*) of 0.20 (equal to a power of 80%), and an added 4 patients due to an expected dropout rate of maximum 5%, a total of 88 patients will be included. The trial is only powered to show relevant differences in the primary feasibility outcome; consequently, results in all secondary outcomes should be considered exploratory only.

#### General Analytical Principles

2.14.2

All analyses will be conducted in the intention‐to‐treat population being all randomised patients except those where outcome data cannot be obtained due to withdrawal of consent [40, 41, 42]. Given the limited sample size and lack of power to assess clinical outcomes, no interim analyses will be conducted to avoid inflating type I error.

#### Outcome Analyses

2.14.3

The primary outcome will be analysed using a generalised linear model with a log‐link and Poisson data distribution according to the relation between variance and mean, and a robust variance estimation adjusted for the stratification variable trial site. Significance of the intervention will be assessed based on the *p*‐value from this regression and reported with the readily available risk ratio with 95% confidence interval. A *p*‐value below 0.05 will be considered statistically significant. A similar analysis, however, with an identity‐link and Poisson data distribution instead to produce the risk difference with 95% CI, will be conducted as well. Dichotomous secondary outcomes will be analysed similarly to the primary outcome; however, no *p*‐values will be reported given the lack of power and explorative nature of these outcomes. Continuous and ordinal secondary outcomes will be analysed using a generalised linear model with an identity‐link, Gaussian data distribution and a robust variance estimation, adjusted for the stratification variable trial site to produce a mean difference with 95% CI. A generalised linear model will be applied, regardless of expected non‐normal data distribution of the residuals. Similarly to the other secondary outcomes, no *p*‐values will be reported.

Additional per‐protocol sensitivity analyses will be conducted for all secondary clinical and process outcomes, excluding patients with one or more protocol violations as defined under secondary feasibility outcome (a).

For the secondary clinical outcome (e) proportion of patients with one or more serious adverse events, a supplemental analysis will be conducted in which death from any cause within 90 days will be included as a serious adverse event.

For the secondary clinical outcome (f) number of days alive without life support, a supplemental analysis will be conducted in which patients who die within 90 days will be assigned a value of 0 days alive without life support.

For the secondary process outcomes (i), (j), and (k), supplemental analyses will be conducted investigating differences in the PaO_2_:FiO_2_ ratio, PaCO_2_ and pH, respectively, between individual baseline and 72‐h measurements.

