## Abstract

Pleural effusions are common in adult intensive care unit (ICU) patients with respiratory failure. Ultrasonography‐guided therapeutic pleural drainage is widely used and associated with improved oxygenation and ventilatory parameters, but no randomised clinical trial data exist. This paper outlines the protocol and detailed statistical analysis plan for the Drainage Of Pleural Effusions in the ICU (DOPE‐ICU) feasibility trial. This is an investigator‐initiated, pragmatic, multicentre, open‐label, randomised, parallel‐group feasibility trial. Adults acutely admitted to the ICU with pleural effusion ≥ 2 cm and respiratory failure will be screened for inclusion. We will exclude patients with existing pleural or mediastinal drain, suspected or confirmed haemothorax, pneumothorax, empyema or pleural malignancy, coagulation deficiency or antithrombotic therapy incompatible with drainage, clinical indication for therapeutic pleural drainage and predefined severe hypoxaemic or hypercapnic respiratory failure, expected ICU stay < 24 h, pregnancy, imminent withdrawal of active therapy, or patients previously randomised in the trial. A total of 88 eligible patients will be allocated 1:1 to ultrasonography‐guided therapeutic pleural drainage with small‐bore catheter, with repeated drainage of repeated pleural effusions during ICU stay including readmissions within 90 days versus no therapeutic pleural drainage during ICU stay within 90 days unless pre‐specified escape criteria apply. The primary outcome is a feasibility outcome assessing group separation, i.e., proportion of patients receiving pleural drainage in ICU within 90 days. Secondary clinical outcomes include all‐cause 90‐day mortality, number of patients with one or more serious adverse events within 90 days, and absolute number of days alive without life support and out of hospital, respectively, in 90 days. Additional secondary feasibility and process outcomes will also be investigated. Data will be compared in the intension‐to‐treat population using generalised linear models adjusted for the stratification variable trial site. ClinicalTrials.gov identifier: NCT06709456. The DOPE‐ICU feasibility trial will assess whether randomised allocation to ultrasonography‐guided therapeutic pleural drainage or not in adult ICU patients with respiratory failure and pleural effusion is feasible. This will inform the design of a future large randomised clinical trial evaluating the clinical effects and safety of pleural drainage in this population.

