#### Secondary Process Outcomes

2.9.3

Proportion of patients with new pleural infection defined as any positive pleural fluid culture of any fungi or bacteria except pre‐defined contaminants being coagulase negative Staphylococci, Enterococci, and *Corynebacterium* species in any pleural fluid sampling conducted after 24 h from randomisation up until 90 days after randomisation.PaO_2_:FiO_2_ ratio in the arterial blood gas analysis (ABG) conducted in ICU closest to 24 and 72 h after randomisation. The FiO_2_ in open systems will be estimated from pre‐specified conversion tables (see Table 2)pH in the ABG conducted in ICU closest to 24 and 72 h after randomisation.PaCO_2_ in the ABG conducted in ICU closest to 24 and 72 h after randomisation.

**TABLE 2 aas70233-tbl-0002:** Conversion tables for calculating FiO_2_ in open systems.

Nasal cannula^a^											
Oxygen flow	0 L/min	1 L/min	2 L/min	3 L/min	4 L/min	5 L/min	6 L/min	8 L/min	10 L/min	12 L/min	14 L/min
FiO_2_	0.21	0.27	0.33	0.37	0.40	0.44	0.48	0.55	0.62	0.64	0.66

High‐flow humidified oxygen^b^																	
Total flow	Percentages represent oxygen concentration in the gas mixture, fractions the corresponding FiO_2_																
	21%	25%	30%	35%	40%	45%	50%	55%	60%	65%	70%	75%	80%	85%	90%	95%	100%
15 L/min	0.21	0.23	0.26	0.29	0.32	0.35	0.38	0.41	0.44	0.47	0.50	0.52	0.55	0.58	0.61	0.64	0.67
20 L/min	0.21	0.24	0.27	0.30	0.33	0.37	0.40	0.43	0.47	0.50	0.53	0.56	0.60	0.63	0.66	0.69	0.73
25 L/min	0.21	0.24	0.28	0.31	0.35	0.39	0.43	0.46	0.50	0.54	0.58	0.61	0.65	0.69	0.73	0.76	0.80
30 L/min	0.21	0.24	0.29	0.33	0.37	0.42	0.46	0.50	0.55	0.59	0.63	0.67	0.72	0.76	0.80	0.85	0.89
35 L/min	0.21	0.24	0.29	0.33	0.38	0.42	0.46	0.51	0.55	0.59	0.64	0.68	0.73	0.77	0.81	0.86	0.90
40 L/min	0.21	0.25	0.29	0.34	0.38	0.43	0.47	0.52	0.56	0.60	0.65	0.69	0.74	0.78	0.83	0.87	0.92
45 L/min	0.21	0.25	0.29	0.34	0.38	0.43	0.47	0.52	0.57	0.61	0.66	0.70	0.75	0.79	0.84	0.88	0.93
> 45 L/min	The FiO_2_ equals the oxygen concentration in the gas mixture																

Hudson mask or similar					
Oxygen flow	6 L/min	8 L/min	10 L/min	15 L/min	30 L/min
FiO_2_	0.45	0.50	0.54	0.59	0.65

Reservoir‐mask (non‐rebreather mask)	
Oxygen flow	≥ 10 L/min
FiO_2_	0.95

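### If an arm has no events, the robust Poisson models fixed for dichotomous secondary outcomes give no usable estimate, and new pleural infection could plausibly meet this

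*Protocol article*

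**What the plan says.** Under Outcome Analyses (2.14.3) the primary outcome is analysed with "a generalised linear model with a log‐link and Poisson data distribution according to the relation between variance and mean, and a robust variance estimation". Trial site enters as a covariate, and the result is given as a risk ratio with 95% CI. A second fit, "with an identity‐link and Poisson data distribution instead to produce the risk difference with 95% CI, will be conducted as well".

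Both carry over to the other binary outcomes: "Dichotomous secondary outcomes will be analysed similarly to the primary outcome". For these the plan omits p-values. Per-protocol versions follow for all secondary clinical and process outcomes. No alternative is named for an arm without events.

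One outcome under this rule, in Secondary Process Outcomes (2.9.3), is: "Proportion of patients with new pleural infection defined as any positive pleural fluid culture". Three contaminant groups are excluded, and only fluid sampled from 24 h to 90 days after randomisation counts. Under 2.7.2, controls are not drained in the ICU unless an escape criterion applies. On trial size, Sample Size Calculation (2.14.1) says "a total of 88 patients will be included", and the Abstract gives 1:1 allocation, so 44 per arm.

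**The concern.** The model suits the primary outcome, which is planned at 40% v 70%. It does not suit a rare binary outcome with 44 per arm. When one arm has no events, the maximum-likelihood risk ratio is infinite (or zero), and the fit simply stops where its convergence rule stops it.

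Usually a huge standard error gives this away. The robust variance removes that warning: the interval comes out narrow and excludes 1 even when the data are one event against none.

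No p-values are reported for secondary outcomes, so the estimates and their intervals carry all the between-group inference. If neither prescribed estimate can be used, the analyst must choose a replacement after seeing the data. A published analysis plan exists to avoid that.

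**Working it through.** **The plan's own figure.** For 40% v 70%, two-sided α 0.05, 80% power and pooled variance:

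n = [1.96·√(2·0.55·0.45) + 0.8416·√(0.24 + 0.21)]² / 0.30² = (1.379 + 0.565)² / 0.09 ≈ 42 per arm.

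That is 84, plus 4 for dropout = 88. The stated size is reproduced, and 44 per arm is used below.

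**Why the interval is narrow.** Take n per arm, no events in control and b in intervention, without site terms. As the fitted control mean μ goes to 0:
- model-based variance of the control log rate: 1/(nμ), which goes to infinity;
- robust variance of the control log rate: nμ²/(nμ)² = 1/n;
- robust variance of the intervention log rate: 1/b − 1/n.

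The robust SE of the log risk ratio therefore tends to √(1/b): 1.00, 0.71 and 0.50 for b = 1, 2 and 4. The point estimate meanwhile runs off without limit.

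**What software prints.** Log link, robust variance, four site terms (four active sites per Trial Status), statsmodels at tolerance 1e-8, every fit flagged as converged. The last three columns use unadjusted methods that tolerate a zero cell.

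| Intervention v control events | Model RR (95% CI) | Fisher p | Newcombe risk difference, points (95% CI) | Score lower limit for RR |
|---|---|---|---|---|
| 1 v 0 | 7.6×10⁸ (1.2×10⁸ to 4.9×10⁹) | 1.00 | 2.3 (−6.0 to 11.8) | 0.27 |
| 2 v 0 | 2.2×10⁹ (6.0×10⁸ to 8.4×10⁹) | 0.49 | 4.5 (−4.1 to 15.1) | 0.54 |
| 4 v 0 | 1.9×10⁹ (7.6×10⁸ to 4.9×10⁹) | 0.12 | 9.1 (−0.6 to 21.2) | 1.09 |

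The size of the RR means nothing. It shifts with how events fall across sites. R defaults give 1.8×10⁸ (4.7×10⁷ to 6.6×10⁸) at 2 v 0, and a tolerance of 1e-6 gives values in the 10⁶ to 10⁷ range. With the intervention arm empty (0 v 4) the RR is 2.6×10⁻¹⁰. The interval excluded 1 in every log-link run. Model-based SEs of the log RR were about 4,000 to 15,000, so the narrow interval comes from the robust variance.

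At 4 v 0 the evidence is borderline. The score statistic at equal risks is (b/44)/√(2·p(1−p)/44) with p = b/88, which gives 1.01, 1.43 and 2.05 for b = 1, 2 and 4. The clearly false exclusions of 1 are therefore those at one or two events.

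**The companion model.** The site-adjusted identity-link Poisson fit failed in every statsmodels run and did not converge in 3 of 4 R runs. The one R fit that converged (2 v 0) gave 3.0 points, against a crude 2/44 = 4.5.

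**How often this could arise for new pleural infection.** The documents give no rate, so these inputs are assumptions: share of controls sampled s = 20–40% (40% is the plan's maximum for control drainage), share of the intervention arm sampled f = 50–100%, positivity among those sampled q = 2–10%, the same in both arms.

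P = (1 − s·q)⁴⁴ × [1 − (1 − f·q)⁴⁴]

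| q | s = 20%, f = 50% | s = 40%, f = 50% | s = 20%, f = 100% | s = 40%, f = 100% |
|---|---|---|---|---|
| 2% | 30% | 25% | 49% | 41% |
| 5% | 43% | 28% | 58% | 37% |
| 10% | 37% | 15% | 41% | 16% |

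Example: s = 20%, f = 100%, q = 5% gives 0.99⁴⁴ × (1 − 0.95⁴⁴) = 0.643 × 0.895 = 0.58. The reverse pattern (intervention empty, control not) is not counted here.

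**The case against.** The strongest reply is that the problem is uncertain, visible and of small consequence.

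- **Likelihood.** A reader might infer that an empty control arm is likely. The documents do not support that. They give no infection rate. Suspected pleural infection is itself an escape criterion, so sampled controls may be enriched for positives. The no-drainage rule covers only ICU stay, whereas the outcome counts any sampling to day 90. Fluid taken at a timely first drainage, within 24 h, does not count, which limits intervention events too. This stands: the case is plausible, not shown to be likely.
- **Visibility.** A reader might infer that the failure is silent and would be published as precise evidence of harm. An RR of 10⁸ from one event is absurd on sight, and the failing risk-difference fit is a second warning. This stands as well. The realistic harm is an unplanned change of method after the data are seen.
- **Scope.** The rule covers every dichotomous secondary outcome, but mortality and the composite serious adverse event outcome should have events in both arms, and the recruitment proportion is not a between-arm comparison. All secondary outcomes are declared exploratory. This stands and limits the severity.
- **Condensed article.** A sparse-data rule might sit in the full protocol. That mitigates but does not settle the point: the article presents itself as containing the detailed analysis plan and states the model without exception.

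**Conclusion.** The point holds for sparse dichotomous secondary outcomes, with new pleural infection and its per-protocol set the clear case. The per-protocol set also removes controls drained outside the escape criteria, which leaves still fewer cultured controls.

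With an empty arm, the prescribed RR has no finite value, its robust interval excludes 1 even at 1 v 0, and the prescribed risk difference usually cannot be fitted. That result does not depend on the assumed rates. How often it would occur does: about 15–58% for an empty control arm with at least one intervention event, under the sampling and positivity assumed above.

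The figure of about 10⁹ should not be quoted as a property of the plan, since it reflects software and tolerance. Severity is minor to moderate.

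**What to change.** Add to 2.14.3: if either arm has no events for a dichotomous secondary outcome, including in per-protocol and supplemental analyses, the model-based risk ratio and risk difference are not reported. Report instead:
- the counts per arm;
- the unadjusted risk difference with a score-type 95% CI (Newcombe or Miettinen–Nurminen);
- a score CI for the risk ratio, open at the undefined end. If both arms are empty, give only the counts and the risk-difference interval.

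Miettinen–Nurminen for both measures has one advantage: the two intervals then agree on whether they exclude no difference. Newcombe for one and a score ratio for the other can disagree, as at 4 v 0 above.

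The cost is one sentence and the loss of site adjustment for the outcomes concerned. Trial Status reports 76 of 88 patients randomised by March 2026, and Strengths and Limitations places publication of the plan before any data analysis, so the rule can still be fixed in advance.

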Side of pneumonia	As estimated by clinicians from radiographic imaging (right‐sided/left‐side/bilaterally).
Multiple trauma	Acute accident with lesions in two anatomical sites or more (yes/no).
Myocardial infarction	Verified by electrocardiographic changes, significant rise in coronary biomarkers, and/or acute PCI or CABG conducted (yes/no).
Cardiac arrest	Clinically diagnosed with initiated cardiopulmonary resuscitation, leading to or occurred during current ICU admission (yes/no).
ARDS	According to the Berlin definition [33] (yes/no).
Sepsis	According to the Sepsis 3 definition [34] (yes/no).
Site(s) of infection^a^	Suspected or confirmed (pulmonary/abdominal/urinary or genital/central nervous system/soft tissue/intravascular/unknown).
SMS‐ICU score [35]	
Systolic blood pressure	Lowest systolic arterial pressure in 24 h prior to randomisation (mm Hg).
Use of vasopressors or inotropes	In 24 h prior to randomisation, includes any continuous infusion of: norepinephrine, epinephrine, phenylephrine, vasopressin analogues, angiotensin, dopamine, dobutamine, levosimendan, or milrinone (yes/no).
Renal replacement therapy	Includes any renal replacement therapy whether chronic or acute, ongoing at the time of randomisation, days between intermittent haemodialysis are considered as with ongoing renal replacement therapy (yes/no).
Chronic co‐morbidity	
Ischaemic heart disease	Previous myocardial infarction, previously conducted PCI or CABG, or previous stable or unstable angina pectoris or use of nitrates indicating this (yes/no).
Chronic heart failure	Chronic LVEF ≤ 40% or diagnosed chronic heart failure with preserved LVEF (yes/no).
Active metastatic cancer	Any metastasis from a malignant non‐haematological neoplasm, which was not considered eradicated at randomisation (yes/no).
Active haematological malignancy	Defined from the World Health Organisation 2017 classification [36], is considered active if the diagnosis resulted in any interventions conducted within the last 6 months prior to randomisation (yes/no).
COPD	Defined as previous spirometry in stable phase diagnostic of COPD [37], or COPD in the anamnesis and daily use of inhaled β_2_‐adrenergic bronchodilators, anticholinergic bronchodilators or glucocorticoids (yes/no).
Chronic dialysis	Includes any renal replacement therapy initiated prior to current hospital admission of any kind, e.g., intermittent haemodialysis or peritoneal dialysis (yes/no).

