#### Missing Data

2.14.5

If less than 5% of data are missing for the primary outcome, a complete‐case analysis will be performed without imputation of missing values. If more than 5% of data are missing, multiple imputation using chained equations will be applied, generating at least 10 imputed datasets under the assumption that data are missing at random [43, 44]. All outcomes and major prognostic baseline variables will be included in the imputation model. Major prognostic baseline variables include: estimated size of the largest pleural effusion (cm), location of pleural effusion ≥ 2 cm (right, left, or bilateral), age, active metastatic cancer, active haematological malignancy, chronic obstructive pulmonary disease, type of admission (medical, elective surgical, or emergency surgical), and SMS‐ICU score. If multiple imputation is applied, the primary trial analysis will be based on the imputed datasets. The unadjusted, non‐imputed (complete‐case) analysis will also be reported. In addition, a best‐worst and worst‐best case sensitivity analysis will be conducted to explore the potential impact of data that may be missing not at random. In the best‐worst‐case scenario, all participants lost to follow‐up in the experimental group will be assumed to have received pleural drainage in the ICU within 90 days, whilst none with missing data in the control group will be assumed to have received pleural drainage. Conversely, in the worst‐best‐case scenario, none of the participants lost to follow‐up in the experimental group will be assumed to have received pleural drainage, whilst all those lost to follow‐up in the control group will be assumed to have received it.

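### 90-day mortality and the two days-alive outcomes are adjusted for trial site only, although a mortality score and baseline life support are collected: a small, avoidable loss of precision

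*Protocol article*

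**What the plan says.** Section 2.14.3 (Outcome Analyses) gives continuous and ordinal secondary outcomes an identity-link Gaussian model with "robust variance estimation, adjusted for the stratification variable trial site to produce a mean difference with 95% CI". This covers outcome (f), days alive without life support, and outcome (g), days alive and out of hospital. Outcome (d), 90-day mortality, comes under a separate sentence in that section that sends dichotomous secondary outcomes to the primary-outcome method. That method is a Poisson model with robust variance and site adjustment, fitted once with a log link for the risk ratio and once with an identity link for the risk difference. The Abstract also names site as the only adjustment variable. None of the supplemental analyses in 2.14.3 adds a prognostic covariate to these three outcomes.

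Randomisation is stratified by site alone (Section 2.1). Table 3 records the type of respiratory support at randomisation. Under the SMS-ICU heading it records lowest systolic pressure, "Use of vasopressors or inotropes" and renal replacement therapy.

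Section 2.14.5 (Missing Data) lists prognostic variables, including age and the SMS-ICU score, but for one purpose: "All outcomes and major prognostic baseline variables will be included in the imputation model". That model is used only if more than 5% of primary-outcome data are missing.

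**The concern.** Severity at entry bears on death and on days alive, and for outcome (f) the link is direct. A patient already on a ventilator, a vasopressor or dialysis at randomisation starts behind, whatever the allocation. With about 42 patients per arm, and severity used in neither the randomisation nor the analysis, a chance difference in severity passes straight into the estimate.

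Section 1 says the trial is to supply preliminary safety and outcome data for the design of definitive trials. These contrasts will be published with 95% confidence intervals even though no p-values are given. If a severity imbalance appears and no adjusted model was fixed beforehand, the only response is a post hoc adjustment in an open-label trial. A risk ratio under a log link and a mean difference under an identity link keep their interpretation when a baseline covariate is added, so adjustment does not change the question being answered.

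**Working it through.** **1. The plan's own figure.** Inputs from Section 2.14.1: "with a type 1 error risk (two‐sided α) of 0.05"; power of 80%; "assuming a maximal incidence of pleural drainage in the ICU within 90 days of 40% in the control group"; a difference of 30 points, so 40% against 70%. With pooled variance and no continuity correction:

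n per arm = [1.96 × √(2 × 0.55 × 0.45) + 0.842 × √(0.40 × 0.60 + 0.70 × 0.30)]² / 0.30² = (1.379 + 0.565)² / 0.09 ≈ 42.

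That gives 84, and with "an added 4 patients due to an expected dropout rate of maximum 5"% the total is 88, as stated. Nothing below changes this. I use 84 patients, 42 per arm.

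**2. Chance imbalance.** The standardised difference in a baseline covariate between arms has standard deviation √(2/42) = 0.218. The chance of a difference above 0.2 SD is 36%, and above 0.3 SD it is 17%. For a binary factor present in 30-50% of patients, the chance of a gap of 10 points or more is 32-36%.

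**3. Gain for the days-alive outcomes.** The site-only model has treatment, intercept and three site terms (four sites, Section 4.1), leaving 84 − 5 = 79 residual degrees of freedom. Adding k covariates that explain a share R² of the variance gives

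SE ratio = √[(1 − R²) × 79/(79 − k)].

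| Assumed R² | k = 1 | k = 2 | k = 10 |
|---|---|---|---|
| 0.10 | 0.955 | 0.961 | 1.015 |
| 0.20 | 0.900 | 0.906 | 0.957 |

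With one covariate, 84 patients carry the information of about 84/0.955² = 92 to 84/0.900² = 104. Ten added terms, roughly the full list in Section 2.14.5, lose most or all of the gain. A worthless covariate costs √(79/78) − 1 = 0.6% by the formula and about 1.5% in the simulation in step 4. I take the larger figure.

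In absolute terms, at an assumed SD of 35 days the 95% half-width is 1.96 × 35 × 0.218 = 15.0 days. Multiplying by √(1 − R²) gives 14.2 days at R² = 0.10 and 13.4 days at R² = 0.20.

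**4. Gain for mortality.** Simulation: 84 patients, four sites, no treatment effect, mortality 35-39%, one continuous score, 1,500 runs per row. Entries are the ratio of empirical standard errors, adjusted to site-only. The risk-difference column comes from a linear model and is indicative only.

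| Score AUC | Log risk ratio | Risk difference | Days alive |
|---|---|---|---|
| 0.50 | 1.015 | 1.016 | 1.015 |
| 0.63 | 0.992 | 0.986 | 0.983 |
| 0.72 | 0.964 | 0.940 | 0.930 |
| 0.79 | 0.947 | 0.903 | 0.884 |

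A second simulation, with 35% mortality and sites of 30, 24, 18 and 12, gave log risk ratio values of 0.986, 0.959 and 0.934 at AUC 0.66, 0.71 and 0.76. The reduction on the risk-ratio scale is therefore about 1-7%.

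**5. Can the planned mortality models take a continuous score?** The log-link model can. In simulations of the identity-link Poisson model at about this size and mortality, non-convergence was 2% or less with site only and at least 50% with a continuous score added. Some of the fits that did converge gave negative risks. Other software may do better, but the risk difference needs another route.

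**The case against.** The strongest reply is that nothing here is an error. The model is stated clearly, agrees with the Abstract and adjusts for the one stratification factor. Its estimates are unbiased under randomisation, and its intervals already allow on average for chance imbalance. All of that stands. A reader might infer that the site-only analysis is biased or its intervals invalid; the documents do not support this.

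A reader might also infer that severity imbalance is the main threat to the clinical results. Section 3.1 names lack of blinding and limited sample size as the limitations, and Section 2.14.4 will show baseline variables by arm, so an imbalance would at least be visible. Nor does the list in Section 2.14.5 commit the plan to covariate adjustment: it serves an imputation model.

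The reply adds that the outcomes are exploratory without p-values, that intervals of 15.0 and 13.4 days are similarly inconclusive, and that event rates and SDs for a later design do not improve when a contrast is adjusted. This limits the weight of the point, but it does not remove the case for a nearly free gain in the reported contrasts. Two practical objections hold and shape the remedy: a continuous score cannot simply be added to the identity-link mortality model, and with 76 of 88 patients randomised by March 11th, 2026 (Section 4.1), the published models should stay on view.

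**Conclusion.** The point holds as a minor one about efficiency. For 90-day mortality and both days-alive outcomes the plan fixes site-only adjustment while collecting, and in one case itself naming as prognostic, covariates that would sharpen the estimates. The standard error would fall by roughly 5-10% for the two days-alive outcomes if the covariates explain 10-20% of the variance, and by about 1-7% for mortality on the risk-ratio scale. The documents give no mortality rate, outcome SD, explained variance or score discrimination, so these sizes rest on assumption. With a weak score the gain would vanish or become a loss of about 1.5%. The gain also depends on adding only one or two strong covariates. The primary outcome, its test and the total of 88 are untouched.

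**What to change.** Before any data analysis, add to Section 2.14.3:

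- **Outcomes (f) and (g):** Gaussian identity-link models with robust variance, adjusted for site and SMS-ICU score (continuous), with invasive ventilation at randomisation (yes/no) added for (f). Report the published site-only models alongside.
- **Outcome (d):** add SMS-ICU score to the log-link Poisson model only. Obtain the adjusted risk difference by standardisation from that model, and do not add the score to the identity-link model. Report the site-only risk ratio and risk difference alongside.
- **Missing score components:** state one simple rule, for example filling in the mean over both arms. The imputation trigger in Section 2.14.5 looks only at the primary outcome and would not cover this.

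The cost is one or two extra parameters, about 1.5% on the standard error if the score proves uninformative, one extra estimation step for the mortality risk difference, and two reported versions of three outcomes. All covariates are already in Table 3, so no new data are needed.
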